## Abstract

**Background:**

In Germany, around 2.250 children and adolescents are diagnosed with cancer each year. Despite generally positive long-term survival rates, many patients must cope with late effects of the disease and its treatment. This highlights the need for a well-structured, long-term approach addressing both physical and mental health issues. Currently, the German healthcare system lacks such comprehensive structures. Our study aims to evaluate the effectiveness of a structured, multidisciplinary long-term approach compared to conventional “treatment as usual” (TAU).

**Methods:**

A prospective, multicenter study with ten pediatric university clinics in Germany will be conducted. The cluster-randomization takes place at the clinic level. Children and adolescents who completed their cancer treatment at least five years ago and their parents will be eligible to participate. While the control group (CG) receives TAU, the intervention group (IG) participates in a structured program. This program includes risk-based medical treatment and psychosocial interventions tailored to each patient’s individual needs within a two-month timeframe. The primary outcome is the improvement of self-efficacy. Secondary outcomes are satisfaction with health care, improvement of health-related quality of life (HRQoL), reduction of mental health problems, and improvement of transition readiness.

**Discussion:**

This approach has the potential to optimize the health care for individuals who survived cancer during childhood or adolescence. It addresses the challenges of overuse, underuse, and misuse of health care resources. By considering both medical and psychosocial factors and promoting increased self-efficacy, independent from parental involvement, it may facilitate a smoother transition to adult medicine and enhance adherence to lifelong aftercare. If proven successful, this approach will contribute to the integration of multidisciplinary strategies into standard healthcare practice.

**Trial registration:**

German Clinical Trials Register DRKS00029269. Registered on December 23, 2022.

## Administrative information

Note: the numbers in curly brackets in this protocol refer to SPIRIT checklist item numbers. The order of the items has been modified to group similar items (see http://www.equator-network.org/reporting-guidelines/spirit-2013-statement-defining-standard-protocol-items-for-clinical-trials/).

## Introduction

### Background and rationale {6a}

In Germany, around 2.250 children and adolescents (≤ 18 years) are diagnosed with cancer each year [1]. While long-term survival rates have improved over the last few years, many patients still experience long-term and/ or late effects resulting from the disease and its treatment [2–5]. These effects can affect various organ systems and range from mild and manageable limitations to potentially life-threatening complications, including subsequent neoplasms [2–5]. Additionally, cancer therapy can increase the risk for infertility, cardiac diseases, or metabolic syndrome [2–5]. The prevalence of long-term and/or late effects increases with the time passed since the primary cancer diagnosis and its treatment [6]. Consistently, patients may develop new, chronic diseases even decades after the completion of their cancer treatment. A study of American survivors of childhood and adolescent cancer demonstrated that by the age of 50 years, nearly all individuals (99.9%) experienced chronic health limitations, with 96% reporting severe health limitations [6]. In contrast, the age-matched control group exhibited an average cumulative incidence of 9.2% for all chronic health limitations and 2.3% for severe limitations [6]. Apart from physical health concerns, childhood and adolescent cancer survivors are subject to an elevated vulnerability to mental health issues [7] or reduced health-related quality of life (HRQoL) [8].

Recognizing and managing these long-term and/or late effects is essential for improving the overall health outcomes and HRQoL for cancer survivors across different age groups. To address these challenges, participation in a long-term, risk-adapted, structured healthcare is recommended [9]. Long-term follow-up in this cohort has resulted in benefits such as early detection of diseases and reduced hospitalizations [9]. Additionally, these patients exhibit improved disease awareness, enhanced health-related self-efficacy [10], and a reduced risk of late complications [10, 11]. To address the diversity of potential long-term and/or late effects depending on the cancer itself and the cancer treatment, a multidisciplinary approach involving general pediatricians, pediatric oncologists, and psychosocial professionals is necessary. This approach should be coordinated with general practitioners and pediatricians in outpatient care [12–14]. However, the German healthcare system often faces challenges in addressing long-term and late effects of pediatric cancer survivors [15]. Regional disparities and non-compliance with guidelines may impede the effectiveness of existing programs, alongside with a deficit in psychosocial care. These psychosocial concerns encompass aspects such as reintegration into the peer group, resuming school or training, and transitioning from child to adult health care [16]. Despite the importance of these topics, some institutions inadequately address them due to a lack of psychosocial personnel. Therefore, a nationwide, tailored long-term aftercare program is essential for pediatric and adolescent patients who are at least five years after the end of their acute oncological treatment.

### Objectives {7}

The present study is entitled “Effectiveness of structured, multidisciplinary long-term care for pediatric cancer survivors: study protocol of the multicenter, randomized-controlled AELKI study.” The aim of the AELKI study is to evaluate the impact of structured multidisciplinary long-term care for children and adolescents five years after the end of the cancer treatment compared to a conventional “treatment as usual” (TAU) condition.

### Trial design {8}

The study is designed as a prospective, multicenter, two-arm randomized-controlled trial (RCT) with two parallel groups. Randomization will be performed as cluster-randomization with a 1:1 allocation. The primary objective of this trial is to test the superiority of the intervention group compared to the control group receiving standard treatment. The primary endpoint is the improvement of patients’ and parents’ self-efficacy after two months (T1) and three months (T2) in the intervention group compared to the control group.

## Methods: participants, interventions, and outcomes

### Study setting {9}

This study provides long-term follow-up care to a cohort of patients who have completed their acute oncology treatment at least five years ago. The study will be conducted across ten pediatric university clinics in Germany, including those located in Augsburg, Berlin, Bonn, Erlangen, Essen, Frankfurt, Hamburg, Kiel, Mainz, and Ulm.

### Eligibility criteria {10}

The inclusion and exclusion criteria for participants in this study are as follows:

Inclusion criteria:Children and adolescents ≤ 18 years and at least one parent/caregiverAcute cancer treatment was completed at least five years agoDigital informed consent

Exclusion criteria:Young adults > 18 yearsAcute cancer treatmentInsufficient understanding of the German languageNo digital informed consent

### Who will take informed consent? {26a}

Study nurses and physicians at the participating pediatric university clinics will identify and approach potential participants. Ample time will be provided to individuals to contemplate their participation and voluntarily decide to join the study. Prior to participation, parental/caregiver consent will be obtained through a digital informed consent (“opt-in”). Moreover, all patients aged 16 years and older will also undergo a digital informed consent process.

### Additional consent provisions for collection and use of participant data and biological specimens {26b}

This study will not involve the collection of biological specimens.

## Interventions

### Explanation for the choice of comparators {6b}

The control condition selected for this study is conventional TAU, which represents the standard medical care received by patients in real-world settings. By comparing risk-adapted guideline-based medical care along with psychosocial support to TAU alone, the study aims to evaluate the potential additional benefit of the new treatment in comparison to the existing standard care.

## Intervention description {11a}

### Screening

A local study nurse will screen potential participants in the intervention and control groups based on predefined criteria (see the “Eligibility criteria {10}” section). Eligible individuals will be contacted by mail or phone, providing detailed study information. Prior to participating, all individuals will give informed consent during the clinic’s waiting time before their long-term follow-up appointment.

### Description of the intervention

After providing informed consent, participants in both the intervention group and control group will engage in a tablet-based survey to evaluate primary and secondary outcomes during the clinic’s waiting time.

Participants in the control group receive conventional TAU, while participants in the intervention group receive a structured multidisciplinary intervention. This includes risk-based medical care and additional psychosocial support within the clinic.

#### Risk-based medical care

In the intervention group, physicianss conduct a structured risk stratification in advance. Since there was no specific risk assessment tailored to childhood and adolescence at the study’s initiation, we utilized the existing risk stratification developed for adults [17] with minor adaptations for suitability in this context. Childhood cancer survivors (CCS) are classified into three risk groups (RG) based on their individual risk of developing late effects due to cancer diagnoses and treatments. The low-risk group includes patients with surgeries only (excluding brain tumor patients), patients with acute lymphoblastic leukemia (ALL) and chemotherapy alone (without radiotherapy), and patients with retinoblastoma. The moderate-risk group comprises patients with chemotherapy (excluding ALL with chemotherapy and retinoblastoma) and patients with both chemotherapy and surgery. The high-risk group includes patients who underwent radiotherapy or allogenic stem cell transplantation. Regardless of their risk group, it is recommended that all patients in the study have at least annual, long-term follow-up appointments.

#### Psychosocial support

Before the initiation of the study, discussions with experts in this research field were conducted to identify typical psychosocial topics that families often raise in the oncological aftercare, such as questions about the transition process, health-promoting behaviors (nutrition, physical activity), the prevention of potential morbidities, and the management of the siblings’ needs. In response, materials and flyers addressing these topics were developed in accordance with recently published PanCareSurFup recommendations [18]. The psychosocial intervention is not standardized but tailored to each patient’s needs. Typically, up to four contacts with the psychosocial team over the next two months will be offered, with the frequency determined by individual needs. These sessions can take place in the clinic or via videoconference to ensure the accessibility and a low-threshold approach.

### Criteria for discontinuing or modifying allocated interventions {11b}

There are no predefined criteria for discontinuing or modifying the allocated interventions. The participation in this study is voluntary and can be terminated at any time.

### Strategies to improve adherence to interventions {11c}

The interdisciplinary project teams in Lübeck, Bonn, and Hamburg meticulously developed both medical and psychosocial interventions before the study commenced. For both intervention and control groups, study nurses received comprehensive online training, along with standard operating procedures (SOP´s) for patient documentation using the CentraXX database [19].

#### Only intervention group

Physicians in the intervention group engaged in workshops focused on the iterative development and guideline-compliant risk stratification in long-term follow-up care. Currently, bi-weekly online meetings provide a platform for the physicians to address practical challenges and ensure quality assurance. The psychosocial team in the intervention group underwent a one-day training workshop. Currently, the psychosocial team meets twice a month in intervention groups for ongoing training and discussions on challenges in practice.

#### Only control group

Currently, physicians and study nurses in the control group participate in bi-weekly online meetings to discuss potential challenges during the study and enhance adherence to study participation.

### Relevant concomitant care permitted or prohibited during the trial {11d}

Implementing structured, multidisciplinary long-term care or usual care will not permit additional care other than the usual care or the structured multidisciplinary intervention which includes risk-based medical care and additional psychosocial support within the clinic for pediatric cancer survivors. Medical follow-ups, for example, due to diagnostic results, will be performed as needed both in the structured multidisciplinary intervention and in the usual care.

### Provisions for post-trial care {30}

All participants who take part in both follow-up surveys will receive a voucher of EUR 25 as an incentive. The follow-up surveys take place after two months (T1) and after three months (T2).

## Outcomes {12}

### Primary outcome

#### Self-efficacy 

To measure the self-efficacy of children and adolescents aged 12 years and older and the self-efficacy of the parents, an adoption of the General Self-Efficacy Scale, German Version [20] will be used. The General Self-Efficacy Scale measures the extent to which individuals believe they can influence events in their lives and overcome obstacles. It consists of ten items rated on a four-point Likert scale, with higher scores indicating a stronger belief in one’s own ability to handle challenges and achieve success. To assess self-efficacy in the context of long-term follow-up care, we have added the following instruction for patients, which is also adapted for use as an instruction in the proxy assessment by parents: “You have overcome a cancer diagnosis and have been in follow-up care for some time. Today, we are asking you questions because we are interested in how you handle new situations related to your health. As you answer the following questions, please think about the topics of ‘health’ and ‘health care’ and how well you manage situations associated with these topics.”

### Secondary outcomes

#### Satisfaction with health care

The perceived satisfaction with health care will be assessed with the Health Care Satisfaction module, a proxy report by parents up to 18 years old [21]. This module is part of the broader Pediatric Quality of Life Inventory (PedsQL) measurement system, which evaluates health-related quality of life in children and adolescents. It comprises 24 items with a 4-Point Likert scale organized into 6 subscales, each focusing on a different aspect of health care satisfaction, such as “information,” “inclusion of the family,” “communication,” “professional competence,” and “emotional needs.” Additionally, patients aged 12 years and older will complete an adaptation of the German short form of the Youth Health Care measure—Satisfaction, Utilization, and Needs (YHC-SUN) [22]. This version consists of 7 items organized into three subscales: satisfaction, utilization, and needs.

#### HRQoL

To assess the HRQoL, the core module from the PedsQL will be used. Parents will provide proxy reports for children up to 18 years old, while individuals aged 12 and older will complete self-reports [23]. The module consists of 23 items, which evaluate HRQoL across four domains: physical, emotional, social, and school functioning. Responses are rated on a five-point Likert scale.

#### Mental health problems

Mental health issues will be assessed using the German version of the Strengths and Difficulties Questionnaire (SDQ) [24]. Parents will provide proxy reports for children up to 18 years old, while individuals aged 12 and older will complete self-reports. The questionnaire is a widely used tool for assessing mental health and behavioral problems in children and adolescents. It includes 25 items with a 3-point Likert scale divided into 5 subscales (emotional symptoms, conduct problems, hyperactivity-inattention, peer relationship problems, and prosocial behavior), each designed to measure different aspects of a child’s emotional and behavioral functioning.

#### Transition readiness

An adaption of the Transition Readiness Assessment Questionnaire (TRAQ) GV 15 will be used to assess a young person’s readiness to transition from pediatric to adult health care [25] as a self-report from 14 years onwards. With its 15 items on a five-point Likert scale, it evaluates various aspects of transition readiness, including the ability to manage health care needs independently, and the ability to effectively communicate health needs and concerns with health care providers.

All questionnaires to assess the primary and the secondary endpoints have been validated for reliability and validity and are widely used in both research and clinical settings. Besides, we recorded sociodemographic data in line with the population-based German KIGGS study [26].

### Participant timeline {13}

The participant timeline is depicted in Fig. 1

**Fig. 1 Fig1:**
[figure not shown]
Participant timeline

### Sample size {14}

In the sample size calculation, we use the following assumptions: we expect the standardized effect of intervention versus control on self-efficacy in parents to be medium with a delta of 0.3 based on effect sizes obtained in comparable cohorts assessing similar outcomes. For example, a meta-analysis by Lundahl et al. [27] showed modest advantage of brief motivational interventions in enhancing health behavior and self-efficacy among various medical care settings. We aim for a power of 80% and account for a loss to follow-up of 10%. We assume an intra-cluster correlation (ICC) of 0.022 [28]. Taking varying cluster sizes into account, patients from at least *N* = 10 pediatric university clinics with a total of at least 160 participants have to be included in the study.

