### Recruitment {15}

Each of the ten participating pediatric university clinics is responsible for recruiting its own participants. The recruitment period is 24 months. Prior to the recruitment, each clinic provided the project management team their average number of patients per month. On average, we expect 160 patients to be recruited in 24 months in each clinic. If recruitment difficulties arise, the recruitment period might be extended.

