## Statistical methods

### Statistical methods for primary and secondary outcomes {20a}

For the primary objective regarding the primary efficacy endpoint, the primary hypothesis will be tested using a permutation test adjusted for cluster-level and subject-level covariates in the full analysis set, comprised of all participants who started the intervention. Details will be specified in the statistical analysis plan. The results will be complemented by estimates of the treatment effect using an adequate model that takes intra-cluster correlation into account (e.g., a linear mixed model or generalized estimating equations). As secondary objectives, we use the same model approach in the full analysis set to analyze the differences in the secondary efficacy endpoints.

A sequential testing procedure will be used to maintain a family-wise type I error of 0.05 for primary and secondary endpoints. If the primary endpoint is statistically significant at alpha = 0.05, the secondary efficacy endpoints will be tested. Hence, positive results on secondary endpoints can be interpreted inferentially only if a treatment effect is shown on the primary endpoint (gate-keeping). For all tested secondary endpoints, the significance level will be adjusted for multiple testing. The preliminary analysis plan is available upon request. The comprehensive analysis plan is currently being written and will be accessible in the German Clinical Trials Register once completed (https://drks.de/search/en/trial/DRKS00029269).

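### The stated total of 160 participants does not give the stated 80% power: with the plan's own inputs it gives about 27–35%, and 160 is probably a per-clinic figure printed as the total

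*Protocol article*

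**What the plan says.** The protocol article, Sample size {14}, gives these inputs:

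- a standardized effect on "self-efficacy in parents to be medium with a delta of 0.3";
- "We aim for a power of 80% and account for a loss to follow-up of 10" per cent;
- "We assume an intra-cluster correlation (ICC) of 0.022".

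It says that unequal cluster sizes were allowed for, without giving a coefficient of variation (CV). It concludes that at least ten clinics "with a total of at least 160 participants have to be included in the study".

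Recruitment {15} states: "On average, we expect 160 patients to be recruited in 24 months in each clinic". Over ten clinics that is 1,600, ten times the stated minimum.

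Sequence generation {16a} divides the clinics five to five. Under Statistical methods {20a}, "the primary hypothesis will be tested using a permutation test adjusted for cluster-level and subject-level covariates", at alpha 0.05. The article does not say whether the test is one- or two-sided, or how much the covariates are expected to gain.

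**The concern.** A total of 160 over ten clinics is 16 per clinic, or 80 per arm before dropout. An effect of 0.3 SD already needs more than twice that per arm under individual randomization, before any allowance for clustering or loss. The stated size and the stated power therefore cannot both be right, and the next section gives a number ten times larger.

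The 160 is the only minimum enrolment in the article. Recruitment {15} allows for difficulties, and a minimum that is far too low could then be read as a target met. At 160 in total the chance of missing the assumed effect would be roughly 65–73%. Because secondary endpoints are tested only if the primary endpoint is significant, inference on all of them would be lost too.

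**Working it through.** **Inputs.** Effect 0.3 (SD 1), power 80%, loss 10%, ICC 0.022 and ten clinics come from Sample size {14}. Five clinics per arm comes from Sequence generation {16a}, and alpha 0.05 from Statistical methods {20a}. Assumptions: two-sided test unless stated; equal clinics (CV 0) as the best case, with a range shown below.

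**Formulas.** With m analysed per clinic:

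- design effect DE = 1 + ((1 + CV²)m − 1) × 0.022
- effective total n = 10m / DE
- noncentrality = 0.3 × √(effective n) / 2

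Power is read from the normal distribution (critical value 1.96) or from the noncentral t with 8 df (critical value 2.306, for ten clinic means in two arms). A permutation test on ten clinic means, over all 252 five-to-five allocations and without covariates, was also simulated.

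**Attempt to reproduce 160 in total.**

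- No clustering, no loss: 2 × (1.960 + 0.842)² / 0.3² = 174.4 per arm, so 175 per arm or 350 analysed.
- 160 in total with 10% loss: m = 14.4, DE = 1 + 13.4 × 0.022 = 1.295, effective n = 144 / 1.295 = 111, noncentrality 1.58.

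| 160 in total, two-sided, equal clinics | 144 analysed | 160 analysed |
|---|---|---|
| Normal | 35% | 38% |
| t, 8 df | 29% | 31% |
| Permutation, simulated | 27–28% | 29% |

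The more lenient variants also fail, even with all 160 analysed and the normal approximation: 50% one-sided with clustering, 47.5% two-sided without clustering and 60% one-sided without clustering. Covariates explaining half the variance at both levels would give 50% (t, 8 df, 144 analysed) to 64% (normal, 160 analysed). With 144 analysed, the effect detectable at 80% power is about 0.53 SD (normal) or 0.61 SD (t), not 0.3.

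**160 per clinic.** The effective n required for 80% by the normal approximation is 2 × 174.4 = 348.8. Solving 10m / DE = 348.8 with equal clinics gives m = 147, and 146.7 / 0.9 = 163 recruited per clinic, about 1,630 in total. In the other direction, 160 recruited gives m = 144, DE = 1 + 143 × 0.022 = 4.146, effective n = 1,440 / 4.146 = 347 and noncentrality 2.80.

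| 160 recruited per clinic, 144 analysed | Power |
|---|---|
| Normal, two-sided, equal clinics | 79.8% |
| t, 8 df, two-sided, equal clinics | 69% |
| Permutation, two-sided, equal clinics, no covariates | 66.5–67.5% |
| Normal, two-sided, CV 0.3 to 0.5 (assumed) | 77% to 73% |
| t, 8 df, two-sided, CV 0.3 to 0.5 (assumed) | 66% to 61% |
| t, 8 df, one-sided 0.05, equal clinics, no covariates | 82% |

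With unlimited patients per clinic, the noncentrality tends to 0.3 × √(10 / 0.022) / 2 = 3.20. The two-sided t power then stops at 79.9%, so without covariate gain more patients per clinic do not bring this test to 80%.

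**Covariate gain at 144 analysed per clinic (assumed values, two-sided, equal clinics).**

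- 25% of variance explained: 71% if only within-clinic variance falls, 81% if both levels fall (8 df); 67% and 77% with 6 df.
- Baseline (T0) self-efficacy correlated 0.5–0.6 with follow-up, with the ICC unchanged after adjustment: 81–86% (8 df).

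**The case against.** No objection rescues 160 in total: every variant tried falls well short of 80%. The objections that carry weight concern what follows from reading it as 160 per clinic.

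- **Power at 1,600.** A reader might infer that even 1,600 patients give only about 68% with the planned test. The article does not support this. The 67–69% belongs to an unadjusted two-sided test with equal clinics, whereas the planned permutation test is adjusted for covariates and its sidedness is not stated. Adjustment for baseline self-efficacy, or a one-sided test, could take the power above 80%. The higher figures are not secure either: 81–86% assumes that adjustment shrinks between-clinic variance in proportion and uses no degrees of freedom for cluster-level covariates. The sample size section claims no covariate gain, so its 80% cannot be credited with one.
- **Origin of the 160.** A reader might take it as established that 160 is the per-clinic requirement. The near match of 163 and the recruitment section make this likely, but the article does not say it. Unequal clinics are said to have been allowed for, and at an assumed CV of 0.3 the same formula needs 208.7 / 0.9 = about 232 recruited per clinic. The match therefore holds only for near-equal clinics.
- **Stopping early.** That a site would actually stop at 160 overall is speculative, since each clinic is told to expect 160.
- **Choice of covariates.** This may properly be left to the analysis plan, and its absence from the article is no error.

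**Conclusion.** The stated total contradicts its own inputs and the recruitment section, and must be corrected. At 160 in total, two-sided power is about 27–35% with 144 analysed (29–38% with all 160), against the stated 80%. This rests only on the protocol's figures, a two-sided 0.05 test and equal clinics; unequal clinics lower it further, and no plausible change of sidedness or covariate gain closes the gap. Confidence in this part is high.

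That 160 is a per-clinic number is a strong inference, not a fact. If it is, 80% comes from a normal critical value with near-equal clinics. Without covariate gain, the two-sided five-against-five comparison has about 67–69%, or 61–66% (t) at an assumed CV of 0.3–0.5. With covariates the range is roughly 67–86%, depending on variance explained and degrees of freedom. This part is conditional. It shows that the 80% has not been demonstrated for the planned test, not that the trial falls short of it.

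**What to change.** 1. Reconcile Sample size {14} with Recruitment {15}. If 160 is meant per clinic, state 160 per clinic and 1,600 in total. If it is not, give the calculation that leads to the stated number.
2. Restate the power for the covariate-adjusted permutation test with five clinics per arm, naming its sidedness, the assumed clinic-size CV and the assumed covariate correlation. The T0 self-efficacy score, already collected at baseline, is an obvious candidate; the analysis plan can carry the detail.

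The cost is wording in the sample size section and a short recalculation. No patients are needed beyond those the recruitment section already expects. The price is a stated power that may be less favourable than 80%.
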